## Abstract

**Background:**

Venous leg ulcers (VLU) have a prevalence of 1–2% in developed countries, and affected patients are severely and long-term impaired in daily activities, work, and social participation. Evidence-based outpatient treatment based on compression therapy is frequently not implemented. The “Ulcus Cruris Care” project was established to develop a disease management concept to improve outpatient treatment for patients with VLU in German primary care. For this purpose, a multifaceted intervention was conceived consisting of an online training for general practitioners and medical assistants, standardized treatment recommendations, e-learning and print-based information for patients, and a software support for case management. The main aims of the Ulcus Cruris Care intervention are to promote standardized treatment according to current scientific knowledge, to facilitate case management for VLU patients exerted by medical assistants, and to support patient education and participation in the treatment process. The UCC trial was designed to evaluate the effectiveness of the Ulcus Cruris Care intervention.

**Methods:**

The UCC trial is a prospective cluster-randomized controlled multicenter trial. Fifty GP practices are intended to be recruited and randomized 1:1 to intervention or control arm. Patients with venous leg ulcers will be recruited by participating GP practices, to include a total of 63 patients in each arm. The primary outcome is time to ulcer healing. Secondary outcomes comprise number and sizes of ulcers, recurrence, pain intensity according to the visual analog scale, health-related quality of life according to EQ-5D-5L, depressiveness according to Patient Health Questionnaire (PHQ-9), patient satisfaction according to the Patient Assessment of Chronic Illness Care (PACIC-5A) query, and adherence to VLU treatment. The outcome analysis of the UCC trial is accompanied by a health economic analysis and a process evaluation.

**Discussion:**

The UCC trial will evaluate whether the Ulcus Cruris Care intervention may lead to faster wound healing, higher health-related quality of life, and lower use of medical resources. If the intervention turns out to have a positive impact on assessed outcomes, comprehensive implementation in primary care may be considered.

**Trial registration:**

The trial protocol (version 1 as of July 19, 2021) has been registered in the German Clinical Trials Register on August 30, 2021 (DRKS00026126).

**Supplementary Information:**

The online version contains supplementary material available at 10.1186/s13063-021-05944-9.

## Background

Venous leg ulcers (VLUs) have a prevalence of 1–2% of the population in developed countries and account for up to 70% of chronic leg ulcerations [1, 2]. Even with the best treatment, wound healing may take several months, and affected patients are severely impaired in daily activities, work, and social participation resulting in a reduced quality of life and a high prevalence of psychological disorders [3–6].

Compression therapy counteracts venous hypertension as the underlying pathophysiologic cycle of chronic VLU and has been proven to be highly efficient displaying 2 to 4 times higher healing rates after 12 weeks compared to wound therapy not routinely based on compression [7, 8]. Although compression therapy represents the pillar of evidence-based therapy, it is not applied in a significant proportion of affected patients. Care analyses in Europe show that only 30 to 50% of patients with VLU receive compression therapy [9, 10]. In addition, if applied, devices and modalities of compression are often not chosen adequately to facilitate an exerted pressure of 30–40 mmHg needed for efficient support of venous reflux [11].

As a consequence, affected patients might have to endure prolonged healing processes. Shortcomings in VLU treatment are presumably of multifactorial nature. In recent years, emerging wound dressing technologies strongly shifted the focus of chronic wound treatment to local wound therapy, although there is no firm evidence for a superior wound dressing for VLU [12]. Insufficient knowledge about compression devices and practical application on caregiver-side has been indicated by observational studies [13, 14]. On the other hand, treatment strategies focusing on local wound therapy may promote that patients tend to assume a rather passive role. This is reflected by lacking patient-sided knowledge about VLU therapy [15]. Since patients may have difficulties to tolerate and handle compression devices, passive role and lacking knowledge may compromise adherence.

The “Ulcus Cruris Care” project was established to develop and evaluate an evidence-based and patient-centered disease management concept to improve outpatient treatment for VLU patients in German primary care. According to known disease management concepts, such as for diabetes mellitus or heart failure, the “Ulcus Cruris Care” project aims to establish a disease-specific standardized case management for patients with VLU in general practices. For implementation into practice, a multifaceted intervention was developed consisting of a training for general practitioners (GPs) and medical assistants, standardized treatment recommendations, e-learning and print-based information for patients, and a software tool supporting wound documentation and case management. The main aims of the Ulcus Cruris Care intervention are to promote standardized treatment of VLU according to current scientific knowledge, to facilitate case management for VLU patients exerted by medical assistants, and to support patient education and active participation in the treatment process.

The UCC trial is intended to evaluate the effectiveness of the “Ulcus Cruris Care” intervention for the treatment of patients with VLU compared to usual care in German primary care practices.

## Methods

### Trial design

The UCC trial is a prospective cluster-randomized controlled multicenter trial designed to evaluate the intervention “Ulcus Cruris Care.” Fifty GP practices in the federal state of Baden-Wuerttemberg are intended to be recruited by the study center, the Department of General Practice and Health Services Research (University Hospital Heidelberg, Germany), and randomized 1:1 to intervention or control arm. Patients with VLU will be recruited by the participating GP practices, to include a total of 63 patients in the intervention arm and 63 patients in the control arm. The study hypothesis is that implementation of disease management for VLU patients in GP practices according to the “Ulcus Cruris Care” intervention can lead to faster wound healing for affected patients. The trial is accompanied by a health economic analysis and a process evaluation to assess the cost-effectiveness and applicability of the intervention. The SPIRIT reporting guidelines were followed for the preparation of the study protocol (see Additional file 1) [16]. Figure 1 offers an illustration of the trial scheme.

**Fig. 1 Fig1:**
[figure not shown]
Trial scheme of the UCC trial

### Study population and eligibility criteria

Approximately 800 regional GP practices collaborating with the study center will be approached by information letters. Interested GP practices will be screened for inclusion by investigators from the study center according to eligibility criteria for GP practices shown in Table 1.

**Table 1 Tab1:** Eligibility criteria for GP practices

Inclusion criteria	Exclusion criteria
• At least one medical assistant is routinely involved in chronic wound treatment and care	• No involvement of medical assistants in chronic wound treatment and care
• IT requirements for using the CareCockpit software met	• GP practices with more than 20 VLU patients per year
	• IT requirements for the use of the CareCockpit software not met
	• no declaration of consent given

*VLU* venous leg ulcer

Eligible physicians and medical assistants will be introduced to the trial via an information sheet and telephone contact for informed consent. Included GP practices are intended to recruit patients with at least one florid venous leg ulcer. Screening and review of patient eligibility will be performed by the responsible primary care physicians of included GP practices. Patient eligibility criteria are shown in Table 2.

**Table 2 Tab2:** Eligibility criteria for patients

Inclusion criteria	Exclusion criteria
• Patient with VLU or mixed ulcer of predominantly venous origin	• Florid leg ulceration of other origins
• Ulcer duration ≤ 6 months	• Ulcer duration > 6 months (182 days)
• Age ≥ 18 years	• Ankle Brachial Index of affected lower extremity < 0.5 or ankle artery pressure < 60 mmHg
	• Decompensated heart failure (≥NYHA III)
	• Immobility
	• Age < 18 years
	• No ability to give consent

*VLU* venous leg ulcer

### Recruitment and trial timeline

Recruitment of 50 GP practices is planned to be accomplished by the end of the 2nd quarter of 2022. All included practices will screen patients likely to meet eligibility criteria and may include a maximum of up to 5 patients. Patients will be directly informed for consent by participating physicians and a patient information sheet. There will be a financial compensation for participants (GP practices and patients) for each study visit and an additional disbursement for complete data collection. Patient recruitment will be monitored by the study center and stopped as soon as the recruitment target of 63 patients is reached in each study arm. The trial timeline is shown in a SPIRIT figure (Additional file 2).

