### Randomization

Included GP practices will be allocated in a 1:1 ratio to either intervention or control arm via cluster-randomization with variable block length. Randomization sequence will be generated using SAS software and is only accessible to the responsible study biometrician of the Institute of Medical Biometry, University Hospital Heidelberg, Germany.

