### Intervention

Ulcus Cruris Care is a multifaceted intervention aiming to implement a disease management concept for outpatient treatment of VLU patients in GP practices. The intervention comprises four major components shown in Table 3.

**Table 3 Tab3:** The intervention components in “Ulcus Cruris Care”

Components of the intervention “Ulcus Cruris Care”	
1	Online training and e-learning courses for GP practices
2	Standard operating procedures for VLU treatment
3	Software support for VLU disease management
4	E-learning courses and printable information for patient education

*VLU* venous leg ulcer

Participating GPs and medical assistants will receive joint online training via webinar according to a synchronous concept comprising 2 teaching units of 45 min each. In addition, asynchronous target-group-specific e-learning courses are provided via an online platform (https://welearn.academy). Online training and e-learning are mandatory to be completed before inclusion of the first patient and will be tracked via documentation and within the online platform. The didactic interventions are designed to support the implementation of a standardized disease management process for VLU patients in GP practices. Under GP supervision, medical assistants are intended to take a central role in wound treatment and patient monitoring and education. Central learning content comprises wound assessment, compression therapy, local wound therapy, and patient education. As a secondary learning objective, practical skills of correctly applying and assessing a compression bandage are to be conveyed. An online video demonstrating the application of compression bandages is integrated in the e-learning course, which is online available at any time. Online training and e-learning courses were designed and reviewed by physicians from the department for general practice and the department for dermatology at the University Hospital of Heidelberg.

To support standardized treatment, the practices are provided with standard operating procedures based on current guidelines for medical compression therapy, wound cleaning and local wound treatment for VLU.

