### Allocation concealment and blinding

Due to the character of the intervention, blinding of GP practices and patients is not feasible. Participating patients will not actively be informed about the allocation of their treating GP practice. However, it may be recognized if patients receive printable information material or access to patient e-learning as a part of the intervention. Investigators analyzing the primary outcome are blinded to group allocation.

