## Discussion

The UCC trial is the first study to evaluate a disease management concept for the treatment of VLU. The Ulcus Cruris Care program was developed to support standardized evidence-based and patient-centered treatment of VLU in GP practices. Its intervention elements are intended to enhance the knowledge and practical skills of caregivers, support standardized treatment of VLU, and promote informed and active participation of patients. As an inherent objective, Ulcus Cruris Care is intended to promote the application of compression therapy by supporting knowledge on the caregiver side and patient adherence, which are the main barriers to its use [13, 15, 23].

With regard to limitations, it has to be mentioned that allocation concealment for participating patients is not feasible. Patients will not be informed about the allocation of their treating GP practice; however, patients in the intervention group receive access for e-learning and print-based information. Furthermore, patient recruitment may be affected by the ongoing COVID-19 pandemic. However, to ensure its feasibility, timelines and recruitment aims have been adapted according to our experiences in currently ongoing studies.

The UCC trial will help to evaluate whether the Ulcus Cruris Care intervention may lead to faster wound healing, a higher health-related quality of life and a lower use of medical resources. If the intervention turns out to have a positive impact on assessed outcomes, comprehensive implementation in primary care may be considered. Furthermore, if successful, the concept of Ulcus Cruris Care may serve as a role model for further disease management concepts for chronic wound treatment.

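### Unblinded practice physicians choose whom to enrol, and only intervention practices must finish training first, so enrolment can differ by arm and can bias the primary hazard ratio in either direction

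*Protocol article*

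**What the plan says.** The unit of randomisation is the practice: "Included GP practices will be allocated in a 1:1 ratio to either intervention or control arm via cluster-randomization with variable block length" (Randomization). Entry of patients is then in the hands of that practice. Under Study population and eligibility criteria, "Screening and review of patient eligibility will be performed by the responsible primary care physicians of included GP practices". Under Recruitment and trial timeline, "All included practices will screen patients likely to meet eligibility criteria and may include a maximum of up to 5 patients", and "Patients will be directly informed for consent by participating physicians and a patient information sheet".

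Those physicians know their arm: "Due to the character of the intervention, blinding of GP practices and patients is not feasible" (Allocation concealment and blinding).

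The two arms do not start from the same line. For intervention practices, "Online training and e-learning are mandatory to be completed before inclusion of the first patient" (Intervention). The Control section gives control practices no intervention, so they have no such condition to meet.

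The article's remarks on concealment concern the patient. The blinding section considers whether patients might recognise their practice's allocation. The Discussion gives as a limitation that "allocation concealment for participating patients is not feasible". Neither place mentions that the person selecting the patients knows the allocation.

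**The concern.** Randomising practices balances practices, in expectation. It does not balance the patients whom practices enrol if the recruiter already knows the arm. Two routes to a difference can be read from the text.

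- **Choice by the recruiter.** A physician who knows the arm decides which likely patients to screen, approach and include. The article sets a maximum but no rule for which eligible patients fill it.
- **A condition in one arm only.** An intervention practice that does not finish training cannot enrol, while a comparable control practice can. Even where training is finished, it can delay the first patient in one arm, which can shift ulcer duration at entry and season.

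At stake is the primary comparison, time to ulcer healing. A prognostic difference created at entry is carried into the hazard ratio, and no analysis can fully remove it afterwards if the relevant factors were not recorded.

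**Working it through.** **1. Order of allocation and enrolment.** Training is an intervention component (Table 3), so a practice receives it only after allocation, and it must precede the first patient. In the intervention arm, enrolment therefore follows allocation. No sentence gives the order for control practices. Trial status has practices recruited from the 4th quarter of 2021 to the end of the 2nd quarter of 2022, and patients during 2022. That calendar fits the same order but does not prove it, and the trial scheme and SPIRIT figure are not shown.

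**2. Room for choice.** With 25 practices per arm and a cap of 5, there are 25 × 5 = 125 places per arm for 63 patients, so 63/125 = 50% are used. The planned mean is 126/50 = 2.5 patients per practice (126/42 = 3 without the reserve practices). Practices with more than 20 venous leg ulcer patients a year are excluded, so 20 is an upper bound on volume, not a typical figure.

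**3. The plan's sample size reproduces.**
- Exponential healing, 60% against 80% at 12 weeks: HR = ln(0.2)/ln(0.4) = 1.756, log HR 0.563.
- Events for 80% power at two-sided 5%: 4 × (1.960 + 0.842)² / 0.563² = 99 (Schoenfeld), or 105 (Freedman).
- Weekly healing rates are 0.0764 and 0.1341. If 20% drop-out accrues over 52 weeks, the probability of an observed event is 0.933 and 0.968, mean 0.950.
- Patients per arm: 99/0.950/2, rounded up to 53, or 105/0.950/2, rounded up to 56. The plan states 55.
- Design effect 1 + (3 − 1) × 0.05 = 1.1; 55 × 1.1 = 60.5, hence 61, rounded up to 21 practices of 3 = 63 per arm.

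**4. Sensitivity of the primary test (illustration).** Assumed, not in the documents: no true effect; a prognostic difference between the enrolled groups, left after adjustment, equivalent to a hazard ratio h; and 95 to 120 events. The upper figure is 126 × 0.950 = 120; the lower is about three quarters of 126. Then

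SE(log HR) = (2/√events) × √1.1 = 0.215 at 95 events and 0.192 at 120.

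Chance of a significant result favouring the intervention = P(Z > 1.96 − ln(h)/SE).

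| h | ln(h) | 95 events | 120 events |
|---|---|---|---|
| 1.00 | 0 | 2.5% | 2.5% |
| 1.05 | 0.049 | 4.2% | 4.4% |
| 1.10 | 0.095 | 6.5% | 7.2% |
| 1.15 | 0.140 | 9.5% | 10.9% |
| 1.20 | 0.182 | 13.3% | 15.7% |
| 1/1.15 = 0.87 | −0.140 | 0.5% | 0.4% |

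For scale, ln(1.15) is 0.140/0.563 = 25% of the planned log HR.

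The last row is selection against the intervention. If the planned effect were true, power at 120 events would fall from P(Z > 1.96 − 0.563/0.192) = 84% to P(Z > 1.96 − (0.563 − 0.140)/0.192) = 60%.

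**5. What the stated safeguards reach.** Blinded photo verification acts on the outcome. The fixed effects (ulcer size, duration of the ulcer, BMI) act on those three factors. The practice random effect models correlation within practices, not a systematic difference between arms in who is enrolled. Expected adherence, mobility and arterial involvement within the permitted range are not in the model.

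**The case against.** The strongest reply is that this is a risk and not an observed imbalance. Eligibility has objective limits common to both arms (duration, age, ankle-brachial index, ankle pressure). The plan expects fewer than the cap per practice and itself fears recruitment bottlenecks; if eligible patients are scarce, there is little to choose from. The webinar is short (two 45-minute units, plus e-learning of unstated length), both arms are paid per visit, and 50 practices are recruited where 42 are needed. The model adjusts for three prognostic factors, and recruitment is monitored centrally. A full protocol exists and may contain a consecutive-enrolment rule or a screening log.

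Much of this stands. It limits the likely size of the effect, and absent screening forms are not in themselves a fault of an article. It does not remove the point. The enrolment mechanism is described, recruiters are unblinded, the training condition applies to one arm, and the limitations name a different problem. Spare practices replace numbers; they do not correct selection.

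Three stronger readings are tempting and not supported:

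- A reader might infer that the hazard ratio is biased in favour of the intervention. Nothing shows that a bias exists or which way it would run.
- A reader might infer that training changes how venous origin is judged, since eligibility includes mixed ulcers that are mainly venous. The listed content includes wound assessment but does not mention differential diagnosis, so this is conjecture.
- A reader might take 11% as the expected error rate. It is one point (h = 1.15) in an assumed range, in one direction.

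**Conclusion.** The concern holds as a structural risk to the primary comparison. Physicians who know the arm decide who enters, and a condition on enrolment applies in one arm only. For the intervention arm this follows from the text; for control practices, enrolment after allocation is an inference. The result can be biased in either direction. The range of about 4% to 16% for the false-positive chance rests wholly on an assumed residual hazard ratio of 1.05 to 1.20, 95 to 120 events and a design effect of 1.1. It shows how sensitive the test is and does not estimate what will happen. The sample size is unaffected. Entry cannot be repaired at the analysis stage, so the remedy belongs in the recruitment procedure.

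**What to change.** 1. In Recruitment and trial timeline, replace the bare maximum of five with enrolment of consecutive eligible patients up to that cap. Keep a one-page screening log in both arms: eligible, approached, refused, reason, ulcer size and ulcer duration. If the full protocol already has such a rule, say so in the article.
2. Open enrolment at the same fixed interval after allocation in both arms, long enough for training to be completed.
3. Report by arm the number of practices that enrol nobody, and the numbers screened, eligible and enrolled.
4. In the Discussion, name selection by the unblinded recruiter as a limitation, separately from patients' awareness of allocation.
5. Where feasible, have practices list their current eligible patients before allocation is released. This does not cover ulcers that arise during 2022, so it supplements item 1 and does not replace it.

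The cost is the log and a short delay before control practices start.

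Central review of baseline photos and ankle-brachial index is not recommended. It adds reading work, and the documents do not show that the photo reviewers could confirm venous origin that way.

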### Randomization

Included GP practices will be allocated in a 1:1 ratio to either intervention or control arm via cluster-randomization with variable block length. Randomization sequence will be generated using SAS software and is only accessible to the responsible study biometrician of the Institute of Medical Biometry, University Hospital Heidelberg, Germany.

